##### Coding process

All video recordings will be stored and coded in Research Cloud. There will be three major aims of coding. The first is to provide information regarding the degree to which the girls participated in problem talk. The second aim is to provide information regarding how girls responded to friends’ statements about problems and/or worries. The third aim is to provide information about the topics on which girls co-ruminate. A team of two coders (both PhD students) will code the data. The coders will first obtain interrater reliability based on 25% of the interactions and then individually code the remaining interactions.

To determine how often girls participate in problem talk, all thought units that the girls produced will be coded as Own-Problem Statements, Friend-Problem Statements, or Non-Problem Statements. To do this, interactions in the PTT will be first transcribed by students of Developmental Psychology of VU Amsterdam and then segmented by the PhD students into thought units, or logical divisions of speech identified based on contextual and syntactic clues, such as pauses, changes in ideas, or changes in who was speaking [68, 69]. Coders will first classify all thought units according to whether they are Own-Problem Statements (i.e., statements about the speaker’s own problems) or not. Next, the thought units will be classified according to whether they are Friend-Problem Statements (i.e., statements about the speaker’s friend’s problems) or not. Each girl will be given a score for the total number of Own-Problem Statements, Friend-Problem Statements, and Non-Problem Statements that they produce.

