Summed scores will be computed for each girl that are the total number of responses of each type that the adolescent produce. The decision to use summed scores for the analyses (as opposed to proportion scores, i.e., the percent of responses of each type out of the total number of responses) is based on the idea that the total number of experiences that adolescents have in which they hear positive engaged, negative or humorous response statements (in other words, the cumulative experience of hearing these responses) should have a particular critical influence on friendships.

Finally, all the problem-focused thought units will then be assigned one of the topic codes. The topic codes were generated a priori based on the literature reviewed regarding challenges during adolescence. Three topic codes are interpersonal: family, peers (nonromantic), and romantic interests. Three are not interpersonal: academics, athletics and other extra-curricular activities, and jobs and money. Finally, each problem-focused thought unit will be timed. The number of seconds that friend dyads spent on each problem topic will be summed. For each step, 25% of the dyads will be double coded. Interrater reliability will be computed separately for T0 and T4.

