Hypothesis 8 “Girls in the intervention group will demonstrate a change in subjects discussed: girls will demonstrate less problem talk about interpersonal problems and shorter periods of interpersonal problem talk immediately after the intervention period and after 1-year follow-up, relative to girls in the control condition” will be tested using Latent Transition Analysis (LTA). Via LTA it can be tested whether girls transition from one class (e.g., a class consisting of girls who engage a lot in interpersonal problem talk; class 1) to another class (e.g., a class consisting of girls who do not engage a lot in interpersonal problem talk; class 2) over time (i.e., between T0 and T4). Via multi-group testing we will investigate whether the probability of changing from class 1 to class 2 is higher for girls in the intervention arm compared to girls in the control arm.

Hypothesis 9 “The hypothesized intervention effects on (the onset) of depression and anxiety symptoms or disorders and depression contagion and anxiety contagion are differently related to changes in interpersonal components of the conversations between girls” will be tested via a joint LTA and DTSA model. First, classes of girls who do and who do not change in their amount and period of interpersonal subjects discussed will be identified via an LTA. Next, it will be investigated whether the resulting classes retrieved from the LTA (i.e., probability of class-membership for the identified transition classes) is a mediator between the intervention effect and the DTSA model of the onset of depression and anxiety symptoms or disorders.

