All analyses will be conducted in structural equation modeling program Mplus (v 8.7 or higher; [106]). Model fit will be determined using the comparative fit index (CFI; critical value ≥ 0.95), the root mean square error of approximation (RMSEA; critical value ≤ 0.06), and the standardized root mean square residual (SRMR; critical value < . 08; [107]). When appropriate, standard errors will be adjusted for clustering of dyads within schools using a sandwich estimator [104]. For hypotheses that include mediation analysis (hypothesis 1 and 5), we will use 10,000 bootstrap resamples with replacement and bias-corrected 95% confidence intervals to test these indirect effects [108]. When appropriate, differences in (indirect) pathways between the intervention and the control arm will be estimated using the DIFFtest option in Mplus (when using the weighted least squares means and variance adjusted (WLSMV) estimator) or the Satorra Bentler chi-square difference test [109]; when using the maximum likelihood estimator with robust standard errors (MLR) estimator).

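### Topic time is summed per dyad, but Hypotheses 8 and 9 use it to classify girls, and no girl-within-dyad adjustment is stated for the latent transition analysis

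*Protocol article*

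**What the plan says.** The Coding process section of the protocol article scores most of the Problem Talk Task per girl: "Each girl will be given a score for the total number of Own-Problem Statements, Friend-Problem Statements, and Non-Problem Statements that they produce". Response types are also totalled for each girl. Topic time is handled differently. First, "each problem-focused thought unit will be timed"; then, "The number of seconds that friend dyads spent on each problem topic will be summed". No duration score per girl is described.

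Under Statistical methods for primary and secondary outcomes, Hypothesis 8 predicts that "girls will demonstrate less problem talk about interpersonal problems and shorter periods of interpersonal problem talk". The test is a latent transition analysis between T0 and T4: "Via LTA it can be tested whether girls transition from one class" to another. A multi-group test then compares the girls' transition probabilities between arms. For Hypothesis 9, "classes of girls who do and who do not change in their amount and period of interpersonal subjects discussed will be identified via an LTA", and class membership becomes a mediator of the onset of depression and anxiety.

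On dependence, the closing paragraph of the same section says that, when appropriate, "standard errors will be adjusted for clustering of dyads within schools using a sandwich estimator". A sandwich estimator for girls within dyads is stated for the survival analysis under Hypothesis 2. The LTA text has no such statement.

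**The concern.** The duration measure has one value per dyad, topic and wave, while the analysis that uses it has girls as its units. Following the text as it stands, the two friends receive identical values on duration. Such a variable has no variation within dyads and cannot act as a girl-level indicator.

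The LTA is also the analysis where the handling of dyads is left unsaid. The growth and cross-lagged models are labelled multi-level, the actor-partner models are dyadic by construction, and the survival analysis of depression onset has its sandwich estimator. The LTA, and the joint LTA and survival model of Hypothesis 9, have none of these.

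At stake is the precision claimed for the arm difference in transition probability, since the duration data hold 160 independent units and not 320. Hypothesis 9 adds a question of meaning: a class driven by a shared duration cannot separate two friends, yet onset is an outcome of the individual girl.

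**Working it through.** **No stated figure is in dispute.** The plan's only sample size calculation concerns depressive feelings (d = 0.50, ICC 0.20, 80 dyads). Assuming two-sided 5% and 80% power, which the article does not state, a cluster-level t calculation gives 39 dyads per arm, or 78 in total, close to the stated 80. It says nothing about Hypothesis 8.

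**Units side by side**

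| Item | Unit in the text | Section |
|---|---|---|
| Statement and response counts | girl | Coding process |
| Timing of speech | thought unit | Coding process |
| Seconds per topic | dyad | Coding process |
| Hypothesis 8 LTA and arm comparison | girl | Statistical methods |
| Hypothesis 9 classes (amount and period) | girl | Statistical methods |
| Onset of depression | girl, with dyad sandwich | Statistical methods |

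**Inputs for the size.** There are 80 dyads (160 girls) per arm (Sequence generation), so 160 dyads and 320 girls in all. Cluster size is m = 2. The ICC is 1 for a value that both friends share.

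**Upper bound.** Assume that the dyad total is given to both girls, that duration alone determines class, and that no clustering adjustment is made.

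- Design effect = 1 + (m − 1) × ICC = 1 + 1 × 1 = 2.
- Effective number of units = 320 / 2 = 160.
- Reported SE / true SE = 1/√2 = 0.707, an understatement of 29%. Equivalently, the true SE is 1.41 times the reported one.
- Type I error at nominal 5% = 2 × (1 − Φ(1.96/√2)) = 2 × (1 − Φ(1.386)) = 0.166.

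**Simulation check.** A two-proportion test stands in for the multi-group LTA comparison, with an assumed class probability of 30% in both arms and 200,000 runs. With each dyad counted twice (160 rows per arm), the type I error was 16.4%. With one row per dyad (80 per arm), it was 5.1%.

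**Below the bound.** If per-girl counts also shape the classes, friends need not share a class and the within-dyad correlation is below 1. The documents give no value for it. Unadjusted, the same formulas give:

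| Assumed ICC | Design effect | Effective units | Type I error |
|---|---|---|---|
| 0.20 | 1.2 | 267 | 7.4% |
| 0.50 | 1.5 | 213 | 11.0% |
| 1.00 | 2.0 | 160 | 16.6% |

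The 0.20 row borrows the ICC for depressive feelings and serves only for scale.

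**The case against.** A reader might infer that the plan enters each dyad twice with the same value and so has a 16.6% error rate. The documents do not support that as a stated step. The article does not list the LTA indicators or describe the data layout. Per-girl seconds could be derived from the planned coding, because each thought unit is timed and speech is divided on cues "such as pauses, changes in ideas, or changes in who was speaking". Hypothesis 8 also covers the amount of interpersonal talk, which can be counted per speaker. The article reports principal features only and refers to an SAP that is not shown.

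On dependence, the Sample size calculation section speaks generally of multi-level models with individuals nested in dyads. The authors also plan a dyad sandwich for depression onset, so they know the issue. The school-level sandwich, if applied, would also absorb within-dyad dependence, since both friends must attend the same school.

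It might also be inferred that the number of latent classes would be chosen with the wrong sample size. The article names no criterion for choosing the number of classes, so that does not follow.

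Most of this stands, and it makes the error rate conditional. It does not remove the conflict. The text does say that seconds are summed for the dyad, and it does name period as part of what defines classes of girls. That is a disagreement between two stated elements, which is more than a detail left to the SAP. The nesting sentence belongs to the sample size section and does not say how a dyad total becomes an indicator for a girl. The school-level adjustment is qualified by when appropriate, and it would correct standard errors without settling the unit of the class.

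**Conclusion.** The point holds as a conflict of units: topic time is defined per dyad, and Hypotheses 8 and 9 use it in an LTA of girls for which no girl-within-dyad adjustment is stated. As written, friends would share the same duration value.

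The 29% understatement of the SE and the type I error of about 16.6% are upper bounds. They require the dyad total to be copied to both girls, class to depend on duration alone, and no clustering adjustment. The effect is smaller if per-girl counts enter the classes, and it is largely removed by a sandwich estimator clustered on dyad or school. The consequences are limited to Hypothesis 8 and the mediation in Hypothesis 9 that depends on its classes.

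**What to change.** Reconcile the Coding process section with the Hypothesis 8 and 9 text before the data are analysed, by one of two routes:

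1. Sum the timed thought units per speaker, so that duration becomes a girl-level score. Cluster the standard errors on dyad in both the LTA and the joint LTA and survival model.
2. Keep the dyad total, and either make the dyad the unit of the duration analysis (80 per arm) or enter duration as a dyad-level indicator in a multilevel LTA.

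Under either route, use the same unit in Hypothesis 9. If the class is defined for the dyad, state how it relates to onset, which is an individual outcome.

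The cost is analysis-plan wording. The first route also needs the seconds totalled by speaker, from units that are already timed. Reported precision will be somewhat less favourable than that of an analysis treating 320 girls as independent.

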### Secondary outcome variables

#### T0, T1, T2, T3, T4, and 1-year follow-up measures T5 (girls)

##### Self-reported (early-onset risk for) generalized anxiety symptoms/disorder

Self-reported generalized anxiety disorder will be measured with the Dutch version of the subscale generalized anxiety disorder (GAD) of the Revised Children’s Anxiety and Depression Scale (RCADS; [70]). This scale has six items (e.g., “I worry about things”) and assesses generalized anxiety on a 4-point scale (0 = *never*, 3 = *always*). The RCADS has good psychometric properties and has demonstrated excellent reliability and validity [70, 71]. We will use the official Dutch translation of the RCADS, which is freely available. The Dutch version of the RCADS—subscale GAD—showed good internal consistency, validity, and sensitivity to change [72].

##### Self-reported problem anxiety talk

Self-reported problem anxiety talk will be measured with the Dutch version of the Problem Anxiety Talk Scale (PATS; [73]). The items are developed to reflect (1) repetitive focus on anxiety‐related topics; (2) threatening interpretations of ambiguous situations; (3) anticipating the likelihood of future negative stressful events; and (4) lack of confidence about successfully coping with stressors. Instructions prompt girls to report on specific verbal interchanges during conversations with their same‐gender best friend with the phrase “When we talk about our worries…” Girls will rate the extent that each item reflects their conversations on a 5‐point Likert scale ranging from 1 (*not at all true*) to 5 (*very true*). Examples of items include “Once I start discussing my worries with my friend, we find it hard to stop,” (i.e., repetitive focus on anxiety‐provoking topics), “My friend often helps me think of possible risks or bad things that might happen,” (i.e., threatening appraisal), “When we discuss bad things that could happen, we talk as if the bad thing will definitely happen” (i.e., likelihood of negative events), and “When my friend and I discuss my worries I start to question my ability to handle future problems. (i.e., lack of confidence in coping skills). The PATS is scored as the sum of all scale items, ranging from 12 to 60 [73]. The PATS demonstrates strong internal consistency (Cronbach’s *α* = 0.89).

##### Self-reported positive and negative affect

Self-reported positive and negative affect will be measured with the Dutch version of the Positive and Negative Affect Schedule for Children (PANAS-C; [74, 75]). The PANAS-C consists of the two subscales Positive Affect (15 items, e.g., energetic) and Negative Affect (15 items, e.g., nervous). Participants are instructed to indicate for each item how often they have experienced that feeling over the past few weeks. Items are scored on a scale ranging from 1 (*very slightly or not at all*) to 5 (*extremely*). The internal reliability of this Dutch version was moderate to good for the Positive Affect subscale (Cronbach’s *α* between 0.66 and 0.83) and for the Negative Affect subscale between 0.67 and 0.81. We will create a dummy variable that represents the type of day (i.e., 0 = *weekend day*, 1 = *weekday*). For the time of day, we will create different dummy variables that represent whether the assessment occurred during the morning (i.e., *morning* = 1, *afternoon and evening* = 0), afternoon (*afternoon* = 1, *morning and evening* = 0), or evening (*evening* = 1, *morning and afternoon* = 1).

##### Self-reported interpersonal responses to positive affect

Self-reported interpersonal responses to positive affect will be measured with the Co-Dampening and Co-Enhancing Questionnaire (CoDEQ; [76]). Items were constructed to assess interpersonal dampening and enhancing responses to happy feelings within dyads and consist of 18 items; nine items will measure co-enhancing and nine items will measure co-dampening. For intrapersonal dampening, the following responses to positive affect are described: thinking about the fleetingness of positivity, thinking about worries, focusing on negative aspects of the positive affect or event, making upward social comparisons (i.e., how others are even better off than you), making external attributions (e.g., thinking “it was just luck”), and starting to think about past negative events. Co-enhancing items were based on the following enhancing responses: behavioral display, focusing on positive feelings (e.g., thinking about how energetic one feels), thinking about positive past and future events, making downward social comparisons (i.e., comparing yourselves to those who are less fortunate), and thinking about positive self-qualities such as the ability to achieve whatever you desire. Respondents must indicate how often they respond in the described way when one of them feels glad or happy and they are talking about this. The rating scale has four response options: *almost never* (1), *sometimes* (2), *often* (3), and *almost always* (4). Cronbach’s alphas were 0.84 and 0.86 for co-enhancing and co-dampening respectively [77].

##### Self-reported quality of the friendship with the dyad friend and investments in the interpersonal relation

Self-reported support quality of the friendship with the dyad friend and investments in the interpersonal relation will be measured with the Dutch version of the Network of Relationships Inventory (NRI; [78]), which includes 36 items. The NRI has seven subscales. The subscale Support consists of eight items. Adolescents and their best friend were instructed to take each other in mind while answering items such as: “How much does your best friend really care about you?”. The subscale Relative Power consists of six items (“To what extent is your friend the boss in your relationship?”). The subscale Negative Interaction consists of sex items (“Are you and your friend annoyed by each other’s behavior?”). The subscale Seeks Safe Haven consists of three items (“To what extent do you visit your friend when you are upset?”). The subscale Provides Safe Haven consists of three items (“To what extent does your friend visit you when she is worried about something?”). The subscale Seeks Secure Base consists of three items (“To what extent does your friend support you in the things you do?”). Finally, the subscale Provides Secure Base consists of three items (“To what extent do you support your friend in the things she does?”). Responses will be rated on a 5-point Likert scale 0 (*little or none*) to 4 (*the most*). The English version of the NRI shows good psychometric properties in adolescent samples, such as high internal consistency and moderately high stability over a 1-year period [79]. Furthermore, in a Dutch sample that used a shorter version of the NRI friend-scales, it was shown that the internal consistencies were high for all variables (Cronbach’s alpha range *α* = 0.82–93) and that the factor and construct validity of the NRI are adequate [80].

##### Self-reported interpersonal reactivity to dyad friend personal distress

Self-reported interpersonal reactivity to dyad friend personal distress will be measured with the Dutch version of Interpersonal Reactivity Index for Personal Distress (IRI-PD; [81, 82]). The IRI-PD consists of seven items (e.g., I’m usually effective in managing stressful situations) and the rating scale ranges from (0) = *describes me not at all* to (4) *describes me very well*. Cronbach’s alpha of observed mean scores showed acceptable values, ranging from 0.67 to 0.87. The psychometric qualities of the Dutch version of the IRI-PD questionnaire were examined by De Corte and colleagues [82]. Cronbach’s alpha was 0.77 [82].

##### Self-reported anhedonic symptoms

Self-reported anhedonic symptoms will be measured with the Leuven Anhedonia Self-report Scale (LASS; [83]). The items tap the consummatory (i.e., reduced pleasure in ongoing experiences), anticipatory (i.e., the diminished pleasure from anticipation to a future positive event), and the motivational (i.e., the decreased drive or motivation to pursue positive outcomes or reward) aspects of anhedonia. Participants will be asked to rate twelve statements according to the last 2 weeks. Example items are: “I found little pleasure in things that I used to enjoy,” “I could get really excited in advance about fun things,” and “I was motivated to do all kinds of things.” The rating scale ranges from *completely untrue* (1) to *completely true* (5). Internal consistency of the total scale is good (*α* = 0.81; [76]).

##### Self-reported mastery

Self-reported mastery will be measured with the Dutch version of the Pearling Mastery Scale (PMS; [84]). The PMS questionnaire contains seven items, each of which is scored on a 4-point Likert scale (1 = totally disagree, 4 = completely agree). A high score reflects a higher degree of mastery. The reliability is adequate (Cronbach’s *α* = 0.78; [85]).

#### T0 and T4 measures (parents)

##### Parental health care use of their child/family

Parental health care use of their child/family will be measured by three questions about whether the child and/or family received health care for psychosocial, emotional, or behavioral problems of the child in the last 12 months, the underlying cause(s), and the duration of the care.

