### Timeline of the intervention and measures

The 14-week HFPM program will be delivered in two cohorts (cohort 1: academic year 2023–2024; cohort 2: academic year 2024–2025) in four phases between February 2024 and May 2025 for both cohorts. The T0 baseline measurements for both cohorts will take place from October 2023 (cohort 1) and from October 2024 (cohort 2), followed by T1 measurements (from February 2024 for cohort 1 and from December 2024 for cohort 2), T2 measurements (from April 2024 for cohort 1 and from February 2025 for cohort 2), T3 measurements (from June 2024 for cohort 1 and from April 2025 for Cohort 2), T4 post-intervention measurements (from September 2024 for cohort 1 and from July 2025 for cohort 2), and a 1-year long-term follow-up measurement (T5) from July 2025 to 2026 (see Fig. 1).

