### Care-as-usual (CAU)

In the control condition, girls receive unchanged CAU including teaching practices they are already exposed to in their current schools. No other classroom-based mindfulness interventions will be implemented during the intervention period of the cRCT.

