##### Participation in the CDI-measures at T0 to T5

Parents/main caretakers will be informed by the PI when girls score > 12 on the CDI-2 (cut-off score for depression) by telephone and will be advised to contact their family doctor or the independent healthcare professional for advice.

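### The T4 question on health care use looks back 12 months although T4 opens only about 9 to 11 months after T0, so it counts pre-baseline and pre-programme care and dilutes the hypothesis 7 comparison

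*Protocol article*

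**What the plan says.** The Protocol article lists health care use under the heading "T0 and T4 measures (parents"). It is measured by three questions: whether care was received, for what cause, and for how long. The period is fixed by the words "received health care for psychosocial, emotional, or behavioral problems of the child in the last 12 months", and no different period is given for T4.

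The section *Timeline of the intervention and measures* gives the dates:
- Baseline: "The T0 baseline measurements for both cohorts will take place from October 2023 (cohort 1) and from October 2024 (cohort 2").
- First wave in the programme: "T1 measurements (from February 2024 for cohort 1 and from December 2024 for cohort 2").
- Post-intervention: "T4 post-intervention measurements (from September 2024 for cohort 1 and from July 2025 for cohort 2").
- Delivery: "in four phases between February 2024 and May 2025 for both cohorts", with no separate start for cohort 2.

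The incentives section gives an earlier date: it rewards app use from November 2023.

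Health care use is a tested outcome. Hypothesis 7 predicts less of it in the intervention arm, and the data analysis plan models its growth rate by arm. The Discussion lists it among the secondary outcomes.

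**The concern.** A 12-month look-back asked less than 12 months after baseline reaches back past baseline. Some care then counts at both waves, so the two answers share months and any change between them is understated. The window also reaches back past the start of the programme, into months in which it could not have acted.

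Hypothesis 7 concerns care during the programme (in the list of hypotheses) and after it (there and in the data analysis plan). On either wording, months before the programme do not belong in the T4 count.

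The listed items do not allow a repair at analysis. Duration says how long care lasted but not when, so an episode that ended before T0 and one that began after the programme can give the same answers. At stake is whether a null result on this outcome could be told apart from a real effect that was watered down.

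**Working it through.** The plan states no figure for the effect on health care use, so there is none to reproduce. The check sets the look-back against the timeline.

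**Inputs from the Protocol article**
- Look-back: 12 months at T0 and at T4.
- Cohort 1: T0 October 2023, T1 February 2024, T4 September 2024.
- Cohort 2: T0 October 2024, T1 December 2024, T4 July 2025.
- Cohort 1 start: February 2024 in the timeline. Trainer training from October 2023 to January 2024 fits this. The incentives section implies November 2023.
- Cohort 2 start: not stated; taken as between T0 and T1.

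**Assumptions**
- Waves take place at their opening dates.
- Care is spread evenly over months.
- The programme lowers care by 30% in exposed months. The documents give no expected effect, so 30% is for illustration only.

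**Step 1. Months counted twice** = 12 − (T4 − T0)
- Cohort 1: 12 − 11 = 1 month (1/12 = 8%).
- Cohort 2: 12 − 9 = 3 months (3/12 = 25%).

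The dates say only when each wave opens, so individual gaps will vary. In cohort 1 the overlap is 0 at a 12-month gap and 3 at a 9-month gap. In cohort 2 it is 5 at 7 months, 2 at 10 months and 0 at 12 months.

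**Step 2. Months in the T4 window before the programme (u)**
- Cohort 1 window opens September 2023. With a February 2024 start, September to January gives u = 5. With a November 2023 start, September and October give u = 2.
- Cohort 2 window opens July 2024. With a start at T0, July to September gives u = 3. With a start at T1, July to November gives u = 5.

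**Step 3. Visible reduction** = 30% × (12 − u)/12

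| u | Exposed months | Visible reduction | Applies to |
|---|---|---|---|
| 5 | 7 | 30% × 7/12 = 17.5% | Cohort 1 (February start); cohort 2 (start at T1) |
| 3 | 9 | 30% × 9/12 = 22.5% | Cohort 2 (start at T0) |
| 2 | 10 | 30% × 10/12 = 25% | Cohort 1 (November start) |

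**Step 4. The same check for a yes/no answer**

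The first item asks about any care, so the proportional formula is only approximate for it. Let λ be a constant monthly rate of first use, assumed to be 1% to 3%, with u = 5:
- Over 12 months, risk ratio = [1 − exp(−λ(5 + 0.7 × 7))] / [1 − exp(−12λ)] = 0.83 to 0.85.
- Over the 7 exposed months only, risk ratio = [1 − exp(−0.7 × 7λ)] / [1 − exp(−7λ)] = 0.71 to 0.72.

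A 28% to 29% lower risk thus shows as 15% to 17%, which agrees with the simpler formula.

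**The case against.** **What stands against the point.** The cohort 1 overlap is fragile, since one month of slippage removes it; cohort 2 is the firmer case. The 5 pre-programme months in cohort 1 depend on the February 2024 start and fall to 2 on the November 2023 date. The size of the dilution rests on an assumed effect and an even care rate, and the duration item could behave differently. Equal 12-month windows at both waves are a defensible choice, because they make the two answers comparable in length. The article gives one short description for both waves, and the T4 form itself is not shown.

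These limit the size of the problem but do not remove it. On the stated dates, pre-programme months remain in both cohorts.

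**Two stronger readings are not supported.**

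A reader might infer that the window biases the arm comparison. It does not by itself: dyads are randomised, so care before T0 and before the programme is balanced in expectation, and use at T0 is measured.

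A reader might also infer that the trial generates the care it counts, and that the comparator is therefore not usual care. The article says "Parents/main caretakers will be informed by the PI when girls score > 12 on the CDI-2", applies a similar rule to the anxiety score, and has parents advised to contact the family doctor or the independent professional. But the rule is common to both arms, and no document says how many parents are called or then seek care. Fewer calls because symptoms fell would be a consequence of the programme, not confounding, while session-based safety contacts exist only in the intervention arm and could work the other way. The statement that control "girls receive unchanged CAU including teaching practices they are already exposed to in their current schools" can be read as describing what the school provides. What remains is a matter of describing the comparator accurately.

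**Conclusion.** The point holds as a mismatch between look-back and timeline that dilutes one parent-reported secondary outcome. On the opening dates, T4 counts again about 3 months of pre-baseline care in cohort 2 and about 1 month, easily lost, in cohort 1. Before the programme lie 3 to 5 of the 12 months in cohort 2, and 5 (or 2 on the November date) in cohort 1.

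An assumed 30% reduction would appear as 17.5% to 25% in cohort 1 and 17.5% to 22.5% in cohort 2, given an even care rate and waves held at their opening dates. No primary outcome is affected. The point is worth correcting because the listed items do not date the care, so the analysis cannot undo the mixing.

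**What to change.** At T4, either ask about care since the T0 questionnaire, or keep the 12-month item and add the start and end month of each episode. Compare the arms on care received after T0, or after a calendar date set per cohort and applied equally to both arms, since control dyads have no programme start of their own. Express it as a rate per month and adjust for the 12-month use reported at T0.

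Dated episodes are the better of the two. Asking since T0 removes the months counted twice but not those between T0 and the programme. In cohort 1 with a February start, 4 of 11 months would still be unexposed, and the illustrative 30% would show as 30% × 7/11 = 19.1%. Dated episodes let the count begin at the chosen calendar date.

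The cost is one reworded parent question or two month fields per episode, with no extra visit. The downside is that the T0 and T4 periods then differ in length, which the monthly rate and baseline adjustment handle. For any cohort already asked at T4, report the result as covering pre-programme months.

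For reporting only, describe the comparator as usual care plus repeated screening with parent notification. The notification rule itself is not questioned. Results should not be split by whether a contact followed a study call, because that conditions on an event after randomisation.
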